**Methods/Design:**

We will conduct a cohort study in eight acute NHS trusts within East of England, with at least one year of follow-up after stroke. The study population will be a systematically selected representative sample of patients admitted with stroke during the study period, recruited within each hospital. We will collect individual patient data on prognostic characteristics, health care received, outcomes and costs of care and we will also record relevant characteristics of each provider organisation. The determinants of one year outcome including patient reported outcome will be assessed statistically with proportional hazards regression models. Self (or proxy) completed EuroQol (EQ-5D) questionnaires will measure quality of life at baseline and follow-up for cost utility analyses.

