## Background

Stroke is the third leading cause of mortality and the number one cause of long-term disability in the UK. More than 150,000 people suffer a stroke in the UK each year [1]. It costs the NHS approximately £ 7 billion per annum [2]. Stroke incidence rises sharply with age and despite better primary and secondary preventative measures, the total number of strokes is set to rise in the UK [3]. Nevertheless, stroke care in UK is far from ideal: patients having a worse outcome in terms of death and dependency than many other European countries [4-6], at least in part due to differences in care provided [7]. There is also variation in outcome between different localities within the UK [8-11], these local differences being highlighted in the most recent publication of the National Sentinel Stroke Audit in 2009 [12]. These differnces probably arise as a result of substantial variations in how the stroke services are provided across the UK. Examples of such differences are access to neurovascular/neurosurgical service, early supported discharge, and stroke specialist on call rota for thrombolysis. The presence or absence of variations in stroke outcomes as a result of variation in care and how much the observed variations in patients' outcomes including patient reported outcome measure (PROM) are determined by the differences in service delivery have not been examined previously.

We hypothesise that variation in patient outcomes including mortality, length of stay, institutionalisation rate, and patient reported outcomes between care providers can partly be explained by the different ways in which stroke services are delivered. The main objectives of the study are (1) to describe variation in outcomes following stroke and to identify the characteristics of services that are associated with better outcomes after accounting for case mix differences and individual prognostic factors, and (2) to obtain preliminary data to identify sample size and inform future pragmatic real world setting RCTs in the area of health service delivery in stroke.

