### Sample size

Since this is an exploratory study designed to provide information for further analytic research, sample size will be determined partly pragmatically rather than on particular hypothesis tests. For illustration purposes, a total sample of 2264 patients would provide 80% power to detect a constant Hazard ratio (HR) of 0.76 for one-year mortality between two groups of roughly equal size, based on the log-rank test. This assumes a 20% one-year mortality rate in the reference group, no loss to follow-up before one year and 2-sided type I error of 5%. If one-year mortality is 30%, then 2264 patients would provide 76% power to detect a HR of 0.81.

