### Plan of investigation

The study will have a cohort design. We will follow up a cohort of patients systematically selected from each trust. For pragmatic purposes we will sample all patients who are admitted every third month, starting from October 2009. Over one calendar month, there will be ~ 300-350 stroke cases entered into the Network Clinical Data. Between October 2009 and September 2011, the Clinical Network would have collected a total of eight 3-monthly datasets per trust (i.e. 8 study months in total: Oct 2009, Jan 2010, April 2010, July 2010, October 2010, Jan 2011, April 2011, July 2011). Therefore, the estimated total cohort size with baseline clinical data will be ~ 2,400 stroke cases during this exercise (30% of 4000 patients admitted annually in 8 trusts = 1200 × 2 yrs).

We will collect patient data by hospital trusts and conduct a questionnaire survey of patients' outcomes. Due to the nature of the study we would need 100% follow-up in randomly selected populations. Because we will be using a partially historical cohort, to avoid selection bias for mortality outcome, informed consent from all eligible participants will not be feasible. Therefore, it is most appropriate for the clinical team to collect the outcome data to comply with current ethical guidance in the UK. Therefore, the identifiable patient data will only be held at the local NHS trusts.

Neither the network nor the investigators will have access to any identifiable patient information (e.g. name, address). For outcome data we will utilise death certificate and hospital episode data from the Patient Administrative System (PAS) as described previously [14,15]. This approach will be used in conjunction with telephone and postal follow-up for questionnaire surveys such as EQ-5 D, and Stroke Impact Scale. These data will be counter-checked using discharge coding records, which record each hospital episode.

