### Statistical analysis

Quantitative data will be analysed by multivariate Cox-proportional hazards to examine the relationships between different aspects of health services and time to death, adjusting for prognostic characteristics. Multiple logistic or linear regression models will be constructed as appropriate for dichotomised and continuous outcome variables respectively. T tests for normally distributed data and Mann-Whitney U tests for non-normally distributed data will be used to compare continuous outcomes. Volume-outcome relationships will be investigated. Missing prognostic and EQ-5 D data will be imputed, based on each patient's other prognostic characteristics. Clustering of data by hospital trust will be investigated and, if necessary, taken into account, and intra-class correlation coefficients calculated to inform future research.

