### Economic Analysis

In the Economic analysis if one option is shown to be less costly and more effective than another option (for example, telemedicine vs. on call system) then that option will 'dominate' the other and be deemed cost-effective. Alternatively, the incremental cost-effectiveness ratio (ICER) associated with a particular option will be estimated and assessed in relation to a range of cost-effectiveness thresholds. The associated level of uncertainty will also be characterised by e.g. estimating the cost-effectiveness acceptability curve (CEAC) for each intervention and conducting value of information analysis [20]. Sensitivity analysis will also be undertaken to assess the robustness of conclusions to key assumptions. We will also seek to identify what resource items should be monitored in a future study (i.e. what are the big cost drivers which are likely to be affected by the intervention) and how these items should be identified.

The study is funded by the NIHR Research for Patient Benefit Programme (PB-PG-1208-18240) and obtained ethical approval from the Norfolk Research Ethics Committee.

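### Allowance for trust depends on a look at the same data, although characteristics fixed for a whole trust need it by design when there are only eight trusts

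*Protocol article*

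**What the plan says.** The Statistical analysis section plans Cox, logistic and linear models relating services to outcome. On correlation within trusts it says "Clustering of data by hospital trust will be investigated and, if necessary, taken into account", and adds that intra-class correlation coefficients will be calculated for future research. It does not say what would count as necessary, how clustering would be investigated or how it would be allowed for.

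The design is a "cohort study in eight acute NHS trusts within East of England". The primary outcome compares one-year mortality between services with different characteristics. Under Plan of investigation, the hospital-level list contains items fixed for a whole trust, such as teaching status, distance from the tertiary centre and surgical specialties on site. A separate patient-level list covers thrombolysis, CT and medication.

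The Sample size section states that "a total sample of 2264 patients would provide 80% power to detect a constant Hazard ratio (HR) of 0.76 for one-year mortality". The illustration there uses a log-rank comparison of two similarly sized groups, and no allowance for trust is made.

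**The concern.** If an exposure takes one value per trust, patients in the same trust add no independent information about it beyond a sharper estimate of that trust's own outcome. Any mortality difference between trusts that neither case mix nor the exposure explains goes straight into the error of the comparison. The study's own hypothesis leaves room for such a difference, since it says variation in outcomes, including "patient reported outcomes between care providers can partly be explained by the different ways in which stroke services are delivered".

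Under the stated rule, a study in which the check happens to be negative falls back on patient-level standard errors, which are too small for these exposures. Eight trusts give such a check few degrees of freedom, while several hundred patients per trust make even a small ICC matter. At stake is the primary comparison for trust-level characteristics, whose results are meant to select interventions for later trials and to inform commissioners.

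**Working it through.** **Inputs from the protocol article.** Eight trusts; N = 2264; hazard ratio 0.76; log-rank test, two equal groups; two-sided 5%; no loss to follow-up; and "This assumes a 20% one-year mortality rate in the reference group". Plan of investigation adds that "the estimated total cohort size with baseline clinical data will be ~ 2,400 stroke cases".

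**Assumptions of mine.** Equal trust sizes, so m = 2264/8 = 283 (2,400/8 = 300 changes little); ICC 0.001 to 0.02 on the one-year mortality scale; trust means approximately normal; four trusts against four.

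**1. The stated power.** With 1132 per group, expected events are 1132 × [p + 1 − (1 − p)^HR], and power is Φ(|ln HR| × √events / 2 − 1.96).
- p = 0.20, HR 0.76: 403 events, power 78.7% (stated 80%).
- p = 0.30, HR 0.81: 624 events, power 74.9% (stated 76%).

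Both agree within two points, so the illustration treats patients as independent.

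**2. Ignoring trust.** The design effect is DE = 1 + (m − 1) × ICC = 1 + 282 × ICC. The type I error of the unadjusted test is 2Φ(−1.96/√DE). At ICC 0.005, DE = 1 + 282 × 0.005 = 2.41 and the error is 20.7%.

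**3. Chance that a 5% check detects the clustering.** This is P(χ²_k > c_k/DE), where c_k is the 5% critical value. Take k = 7 for a check across all eight trusts, or k = 6 for a check within the two groups being compared.

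**4. The conditional rule.** I simulated 1,000,000 sets of eight trust means with no true effect. If the check was significant, the groups were compared with a trust-level t test on 6 df; otherwise with the unadjusted test.

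| ICC | DE | Ignoring trust | Detected, 7 df / 6 df | Conditional rule, 7 df / 6 df | Always trust-level t |
|---|---|---|---|---|---|
| 0.001 | 1.28 | 8.3% | 14% / 13% | 5.7% / 7.3% | 5.0% |
| 0.002 | 1.56 | 11.7% | 25% / 23% | 6.5% / 9.0% | 5.0% |
| 0.004 | 2.13 | 17.9% | 47% / 43% | 6.9% / 10.4% | 5.0% |
| 0.005 | 2.41 | 20.7% | 56% / 52% | 6.8% / 10.4% | 5.0% |
| 0.01 | 3.82 | 31.6% | 82% / 77% | 6.0% / 8.7% | 5.0% |
| 0.02 | 6.64 | 44.7% | 95% / 93% | 5.3% / 6.3% | 5.0% |

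Detection reaches 50% at an ICC of 0.0043 (7 df) or 0.0048 (6 df). A split of two trusts against six gives practically the same error rates.

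**5. Large-sample reference after adjustment.** If the adjusted analysis uses a normal reference instead of t on 6 df, the conditional rule gives 6.4% to 9.9% (7 df) or 7.4% to 11.5% (6 df). Always adjusting, but with a normal reference, gives 5.5% to 9.7%. Removing the condition is therefore not enough without a small-sample method.

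**The case against.** The strongest reply is that the document specifies no test. It says only that clustering will be investigated, and a sensible analyst might use a lenient check. That has force: a 20% check on 7 df followed by the trust-level t test gives 3.7% to 5.0% over the same ICC range, so no excess. With a large-sample reference after adjustment, however, the same lenient check reaches nearly 10%. The text promises neither the lenient check nor the small-sample reference.

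The second reply is that the study is exploratory, is not sized on particular hypothesis tests, disclaims causal conclusions and already plans to report intra-class correlations. This lowers the gravity but does not justify the condition, because the article also expects commissioners to use the results.

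Some stronger readings may tempt a reader but are not supported:
- *That the check usually misses the clustering.* With a 5% test this is so only below an ICC of about 0.0045; at 0.01 detection is about 80%. The documents give no ICC.
- *That error rates of 12% to 45% apply.* Those belong to always ignoring trust when the ICC is 0.002 to 0.02, which the plan does not propose.
- *That every service characteristic is affected.* Thrombolysis, CT and medication vary within a trust, and this inflation does not carry over to them automatically.
- *That the economic results share the fault.* The Economic Analysis section mentions "estimating the cost-effectiveness acceptability curve (CEAC) for each intervention" but does not say that patients will be treated as independent there.

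**Conclusion.** The point holds for characteristics fixed at trust level and for the volume-outcome analyses. It concerns a rule that the article states, not a detail left to a later analysis plan: a plan that merely defined when adjustment is necessary would keep the conditional structure.

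The size is moderate. If the check is a 5% heterogeneity test, type I error is 5.3% to 6.9% (7 df) or 6.3% to 10.4% (6 df), and up to about 11.5% with a large-sample reference, against 5.0% when trust is always accounted for by t on 6 df. These figures rest on the assumed ICC range, equal trust sizes, approximately normal trust means and an assumed form of check. Since the study is exploratory, this should be fixed but does not undermine the study.

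**What to change.** Remove the condition. State that every model of a trust-level characteristic, including volume, will account for trust whatever any test of clustering shows, using a method suited to eight clusters. One example is to estimate a case-mix-adjusted outcome for each trust and regress the eight values on the characteristic, with t on 8 − 2 = 6 df. Report the ICC descriptively and do not use it as a gate.

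No new data, patients or sites are needed, but there is a real cost in precision. Confidence intervals for trust-level effects become wider, and power falls below the patient-level illustration. For HR 0.76, 20% mortality, N = 2264 and four trusts against four, t on 6 df gives about 63% at ICC 0, 46% at 0.002, 32% at 0.005 and 22% at 0.01, against the stated 80%. The Sample size section should say that its figures do not apply to characteristics fixed at trust level.

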### Economic evaluation

Health care resources are scarce and it is therefore important to ensure that evaluations are undertaken in order to ensure that services provided by the NHS constitute value for money. Within this study we will thereby seek to estimate the cost-effectiveness of different stroke service deliveries.

Costs will first be calculated from the perspective of the NHS and personal social services (PSS). Thus, levels of resources use will be recorded during the follow-up period, including the length of original hospital stay, input by the multi-disciplinary team, other investigations (e.g. x-ray) and any complications (including details of any further hospital admissions). Unit costs will subsequently be assigned to each of these resource items, enabling both the total mean cost in participants and the incremental cost between two different service deliveries (chosen to compare the cost effectiveness, e.g. traditional on call rota vs. telemedicine) to be calculated after adjusting for other factors. The main measure of effectiveness to be used in the economic analysis will the EQ-5 D [17], where responses will be sought at baseline, and at 12 month as mentioned above. This will enable the overall effect of each mode of service delivery, and the incremental effect of services to be estimated.

#### Outcome

As the National Institute of Health and Clinical Excellence [18] recommends use of the EQ-5 D [17] within cost-effectiveness analysis this will be our primary measure within the economic analyses. EQ-5 D data will be collected at two University Hospitals and two district general hospitals within the clinical network. We will use "mapping" strategy to estimate the cost-effectiveness analyses across the region. The use of mapping, where scores from a condition-specific (non preference-based) measure are 'converted' into a utility (preference-based) score using a pre-defined formulae, has been advocated (in certain instances) by the UK National Institute of Health and Clinical Excellence (NICE) [18], and has been used to estimate the utility scores, and in turn cost-effectiveness, of a number of health care interventions [19]. Mapping presents the possibility of not asking all participants to complete the EQ-5 D. In this study we propose to take advantage of this by developing a mapping algorithm based on the response from participants participating in this component to predict the EQ-5 D for participants in retrospective cohorts and those who did not participate in PROM component.

Because the quality of life measure (EQ-5D) which can be used to estimate health utility and calculate QALYs (Quality Adjusted Life Years) for economic evaluation is outside the remit of routine data collection and cannot be done retrospectively, we will collect EQ-5 D data in only the second year of the study (October 2010 and January, April and July 2011 cohorts and one year follow up data to be collected September and December 2011, and March and June 2012) in those who provide informed consent to the study (we estimate that the sample will be approximately 15-20% of the whole sample after excluding the one year pre-study period (between October 2009-September 2010) and after taking into account of refusal rate (estimated ~ 30%) in trusts with Stroke or Comprehensive Local Research Network Research Nurses.

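### EQ-5D is to be predicted for about 80-85% of the cohort; if only prognostic characteristics are used, the region-wide utility difference between services is pulled towards zero

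*Protocol article*

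**What the plan says.** The Economic evaluation section makes EQ-5D, at baseline and 12 months, the main measure of effectiveness and says of it: "This will enable the overall effect of each mode of service delivery, and the incremental effect of services to be estimated".

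The Outcome subsection restricts measurement by place, "EQ-5 D data will be collected at two University Hospitals and two district general hospitals within the clinical network", and by time, "we will collect EQ-5 D data in only the second year of the study". It puts the size of the measured group as follows: "we estimate that the sample will be approximately 15-20% of the whole sample after excluding the one year pre-study period", also allowing for refusals of about 30%. For the analysis across the region, a mapping algorithm built on PROM participants is to be used "to predict the EQ-5 D for participants in retrospective cohorts and those who did not participate in PROM component". That subsection describes mapping in general as turning a condition-specific score into a utility. It does not list the algorithm's predictors.

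The Statistical analysis section gives a rule for filling in EQ-5D: "Missing prognostic and EQ-5 D data will be imputed, based on each patient's other prognostic characteristics". The PROM section lists the Stroke Impact Scale, modified Rankin and Barthel scores, together with EQ-5D, as parts of the PROM component.

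**The concern.** A utility predicted from prognosis alone is identical for two patients with the same prognosis who were treated under different services. Among predicted patients, the case-mix-adjusted service difference in utility is then zero by construction, whatever the truth. Pooling these patients with the measured minority dilutes the difference seen in the minority.

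The increment feeds the ICER, the acceptability curves and the value-of-information analysis in the Economic Analysis section. The Discussion says the results will inform commissioners and the design of future RCTs. A service that improves recovery without changing survival could be reported as giving little utility gain.

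**Working it through.** **1. The stated measured share.** Inputs from the article: "the estimated total cohort size with baseline clinical data will be ~ 2,400 stroke cases during this exercise"; EQ-5D in the second year only (4 of 8 study months); 4 of 8 trusts; refusal about 30%. Trust sizes are not given, so four trusts are assumed to take half of admissions.

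2,400 × 1/2 × 4/8 × (1 - 0.30) = 420, and 420 / 2,400 = 17.5%.

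This lies inside the stated 15-20%, read as a share of the whole cohort (360-480 patients). The predicted share is then 80-85%. Read instead as 15-20% of the second-year patients only, it would be 180-240 people, or 7.5-10% of the cohort. The arithmetic does not favour that reading, because 420 is 35% of 1,200.

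**2. Attenuation formula.** Let δ be the true adjusted service difference in non-fatal utility, m the measured share (the same in each service), and f the share of δ carried by the predictors. The article does not give f, so it is varied from 0 to 1. Measured patients show δ and predicted patients show fδ, so

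pooled difference = mδ + (1 - m)fδ, and retained share = m + (1 - m)f.

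| f | m = 0.15 | m = 0.20 |
|---|---|---|
| 0 (prognostic characteristics only) | 15% | 20% |
| 0.25 | 36% | 40% |
| 0.5 | 58% | 60% |
| 0.75 | 79% | 80% |
| 1 | 100% | 100% |

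For an illustrative δ of 0.05, f = 0 gives 0.15 × 0.05 = 0.0075 to 0.20 × 0.05 = 0.010.

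**3. Simulation check.** The simulation used 2,400 patients, two services, 1,500 repeats and an equal measured share in both services. Prognostic predictors alone retained 14.9% (m = 0.15) and 20.0% (m = 0.20). With a post-stroke outcome among the predictors, f = 0.5 retained 57.2% and 60.1%, and f = 1 retained 100.3% and 100.6%. Adding a service term to the prognostic predictors retained 98.6% and 99.0%.

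**4. The mortality part.** Deaths are known for the whole cohort. As an illustration, take HR 0.76 and 20% reference mortality from the Sample size section. Mortality with the better service is 1 - 0.8^0.76 = 15.6%. Assume survivor utility 0.60, a survivor gain of 0.03 or 0.05, death counted as 0, and predicted survivors given 0.60 plus half the gain in both services.

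- Gain 0.03: true difference = 0.844 × 0.63 - 0.80 × 0.60 = 0.052. Retained at f = 0: 60% (m = 0.15) to 62% (m = 0.20).
- Gain 0.05: true difference = 0.844 × 0.65 - 0.80 × 0.60 = 0.069. Retained at f = 0: 49% to 52%.

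A total effect that includes deaths therefore keeps 49-62% under these assumptions, even in the worst case for survivors.

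**The case against.** The strongest reply is that the mapping described in the Outcome subsection is not prediction from prognosis. A condition-specific score taken after stroke care is itself a health outcome. It can carry part or all of the service effect with no service term in the algorithm. The imputation sentence in Statistical analysis does not mention mapping and may be meant for gaps among patients who were asked for EQ-5D. An article may also leave the predictor list to the full plan.

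Much of this stands. A reader might infer that the algorithm excludes service, or that the region-wide increment will shrink to the measured share. The article supports neither as fact: it names no service term but excludes none, and 15-20% is only the f = 0 end of the range. A reader might also infer that intervals will be computed as if all 2,400 patients had been measured. No standard-error method is stated, and uncertainty and sensitivity analyses are planned.

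The reply does not dispose of the point. The candidate source scores (Stroke Impact Scale, modified Rankin, Barthel) are listed as PROM items, whereas the patients to be predicted are those outside PROM. Plan of investigation mentions telephone and postal follow-up with the Stroke Impact Scale, but nowhere says that the retrospective cohorts complete it. Discharge destination, length of stay, complications and readmissions are study-wide secondary outcomes and could raise f, but they are not named as predictors. The one predictor class that is named is the one that produces the full attenuation.

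**Conclusion.** The concern holds conditionally. Applied as written, the prognostic-only rule would leave 15-20% of the true non-fatal utility difference in the region-wide estimate. If the predictors carry half the effect, 58-60% remains. There is no attenuation only if they carry all of it, and the article describes no source score by which that would happen for patients outside PROM.

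These figures assume that 15-20% refers to the whole cohort, that the measured share is equal across services, and that measured and predicted patients are otherwise alike. The equal-share assumption is doubtful, since a service found only in the four trusts outside PROM has no measured EQ-5D.

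It would go too far to conclude that the whole QALY difference collapses, because its mortality part is observed for everyone. The point deserves correction before the economic analysis but does not threaten the study's main result: the study is exploratory, its primary outcome is one-year mortality, and the economic analysis is secondary.

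**What to change.** 1. Reconcile the PROM, Statistical analysis and Outcome sections. State which scores exist for patients outside PROM, which variables enter the algorithm, and whether the prognostic-only rule applies to it.
2. Estimate the incremental EQ-5D effect primarily in patients with measured EQ-5D, with the service characteristic in the model.
3. For any region-wide estimate, include in the prediction model the service characteristic and the cohort-wide post-stroke outcomes (discharge destination, length of stay, complications, readmissions). Use multiple random draws rather than single fitted values, so that the uncertainty reflects the measured patients.
4. State that no utility increment can be estimated for services found only in the four trusts outside PROM.

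This needs analysis work and wording but no new data. The price is wider intervals, since the primary increment would rest on about 360-480 consenting patients in four trusts. Fewer will have a 12-month response: with 20-30% mortality, 420 falls to 336-294. Hospital-level characteristics would be compared across only four hospitals, and a service term cannot remedy that.
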